**Methods/design:**

A total of 120 children aged between 3 and 8 years of age diagnosed with amblyopia in association with either anisometropia or strabismus, or both, will be randomized to receive either a standardized or a personalized occlusion dose regimen. To avoid confounding by the known benefits of refractive correction, participants will not be randomized until they have completed an optical treatment phase. The primary study objective is to determine whether, at trial endpoint, participants receiving a personalized dosing strategy require fewer hours of occlusion than those in receipt of a standardized dosing strategy. Secondary objectives are to quantify the relationship between observed changes in visual acuity (logMAR, logarithm of the Minimum Angle of Resolution) with age, amblyopia type, and severity of amblyopic visual acuity deficit.

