## Methods/design

### Objectives of the study

The primary study objective is to determine whether study participants in receipt of a personalized dosing strategy reach trial endpoint (optimal visual acuity) in a shorter period of time, and with reduced variance, than those in receipt of a standardized dosing strategy.

The secondary study objectives are:To determine the relationship between observed changes in logMAR visual acuity as a function of:Objectively monitored occlusion dose,Type of amblyopia,Age of participant.To determine whether compliance differs between standardized and personalized dosing strategy treatment arms.

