### Dosing strategies

#### Standardized dosing strategy

In the standardized dosing strategy arm, participants are prescribed one of three dosing regimens dependent on their visual acuity at the end of the optical treatment phase. These dosing regimens were the consensus outcome, initially of formal face-to-face discussion, between eight senior orthoptists identified by membership of the British and Irish Orthoptic Society, and drawn from geographically diverse areas of the United Kingdom. All experts had a minimum of 10 years’ clinical experience. Discussion focused on the management of six clinical scenarios representative of cases meeting the RODS eligibility criteria. The experts’ views of how each scenario should be managed were appraised by the panel convener ([name]) and a series of dosing regimens was derived. These regimens were subsequently reviewed by the panel and their suitability unanimously confirmed by all members as follows:Mild amblyopia (<0.4 logMAR): 2 hours per day,Moderate amblyopia (0.4 to <0.8 logMAR): 3 hours per day,Severe amblyopia (≥0.8 logMAR): 5 hours per day.

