#### Personalized dosing strategy

In the personalized dosing strategy arm, participants are prescribed an initial occlusion dose determined by their age, type, and severity of amblyopia, based upon dose-response functions derived from previous studies involving participants of near-identical clinical and demographic status to those enrolled in the present trial [11,12]. As participants in this arm progress through the occlusion phase, the prescribed occlusion dose is modified at each clinic visit, depending on treatment compliance, and is predicated on the notion of a total effective dose: the minimum amount of occlusion that should result in an optimal visual outcome.

The rationale underpinning treatment by a personalized dosing strategy is an attempt to define a patient’s total occlusion dose, which can then be converted to a daily patching regimen on the presumption of a fixed treatment period. We make the assumption that every patient has some optimal visual outcome that they can hope to achieve, and that there exists some total effective dose of occlusion that must be received in order to achieve it. Furthermore, we assume that any dose received by a patient in excess of this total effective dose is ‘wasted’: it does not improve the patient’s visual acuity any further, as it is impossible to improve beyond the patient’s optimal visual outcome. For example, if a patient’s total effective dose is 200 hours, then that patient will have the same visual outcome after 200, 250, or even 1,000 hours of occlusion. However, the patient’s visual improvement would be limited if fewer than this 200 hours of occlusion were achieved. Employing mathematical notation, we can say that patient *i* has some optimal visual acuity *V*_*i*_^***^, which will be achieved if, and only if, patient *i* undertakes at least *D*_*i*_^***^ hours of occlusion. Our aim is to construct a model that predicts this *D*_*i*_^***^ based on an analysis of known treatment-response functions [11,12]. To constrain the complexity of the model (and in the absence of compelling evidence to the contrary) it is assumed that the total effective dose is dose-rate independent, that is, a single occlusion dose is of equivalent effectiveness to multiple individual doses that sum to the same total number of hours.

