Predictions of *D*_*i*_^***^ were derived from a normal linear interval regression model with the total effective dose of some patient *i* with initial residual amblyopia *R*_*i*_ and age *A*_*i*_ estimated by the formula:$$ {\mathrm{D}}_{\mathit{\mathsf{i}}}^{*}={\left(18.150+16.122{R}_i\hbox{--} 0135{A}_i\hbox{--} 0.547{T}_M\hbox{--} 8.028{T}_S\hbox{--} 12.176{R}_i{T}_M\hbox{--} 11.334{R}_i{T}_S+0.065{A}_i{T}_M+0.192{A}_i{T}_{\mathrm{S}}\right)}^2 $$where *T*_M_ and *T*_S_ are indicator functions taking the value 1 if the patient has mixed or strabismic amblyopia, respectively, or 0 otherwise.

In practice, participants in the personalized dosing strategy arm have their total effective dose estimated on an assumed fixed follow-up period of 12 weeks, which results in manageable dose-rates. Therefore, an individual patient’s personalized daily patching regimen will be calculated by first estimating the total effective dose and then dividing this by the number of days left in the follow-up period. For reasons of practicality, we only prescribe daily patching episodes rounded up to the nearest 30 minutes. Dose-rate can then be updated at follow-up appointments based on how much occlusion has been objectively recorded. To avoid the prescription of subtherapeutic doses of occlusion, the model is constrained such that dose-rates less than 2 hours per day are never prescribed. Of course, patients will probably be treated for a period longer than 12 weeks, as the follow-up sessions will be continued until the visual acuity criteria for study exit have been met. Therefore, once a patient passes the tenth week of follow-up, all future daily prescription calculations will assume a 2-week follow-up period until treatment is completed.

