#### Analyses

The primary study objective of comparing time to best visual acuity between the two treatment groups, along with the secondary objective of comparing compliance, will be analyzed via standard *t* tests (to compare length of time and compliance) and Levene’s test (to compare variance in time). Suitable nonparametric alternatives will be used should concerns arise regarding the necessary distributional assumptions for these methods. The secondary objective to determine the relationship between changes in visual acuity and dose, amblyopia type, and age, will be investigated using standard regression modelling approaches.

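### The secondary dose-response regression is stated without baseline severity, which sets the prescribed dose in both arms, and the abstract and body disagree on the factor list

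*Protocol article*

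**What the plan says.** The protocol article states the same secondary objective in three places, with two different factor lists.

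- **Abstract, Methods/design:** change in acuity is to be related "with age, amblyopia type, and severity of amblyopic visual acuity deficit". Dose is not listed.
- **Objectives of the study:** the factors are "Objectively monitored occlusion dose,Type of amblyopia,Age of participant". Severity is not listed.
- **Analyses:** the objective "to determine the relationship between changes in visual acuity and dose, amblyopia type, and age, will be investigated using standard regression modelling approaches". Severity is again not listed.

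The dose rules both depend on severity. In the standardized arm "participants are prescribed one of three dosing regimens dependent on their visual acuity at the end of the optical treatment phase", namely 2, 3 or 5 hours per day by acuity band. In the personalized arm "participants are prescribed an initial occlusion dose determined by their age, type, and severity of amblyopia". The prediction formula there contains "initial residual amblyopia" (R) and its interactions with type. The Background also says that earlier studies found dose-response to vary with type, age and severity.

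**The concern.** The two factor lists cannot both describe the planned analysis. The list that the body carries into the Analyses section is the weaker one. Of the three characteristics that set the personalized dose (age, type, severity), it keeps two and drops the third. In the standardized arm it drops the only one.

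Severity also acts on the outcome. A child exits when the eyes reach equal acuity or vision stabilizes (Endpoint determination and sample size calculation), so a small starting deficit leaves little room for gain. A variable that raises both dose and gain, if left out, lends its effect to dose. The secondary objective could then report a dose-response slope that is partly or wholly a severity effect.

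**Working it through.** **1. Severity drives the prescribed dose.** The total effective dose for an anisometropic child reduces to D = (18.150 + 16.122R − 0.135A)², with A in months. The age coefficient is printed without its decimal point; reading it as 0.135 reproduces the article's worked example.

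- R = 0.5, A = 48: (18.150 + 8.061 − 6.480)² = 19.731² = 389.3 h. Divided by 84 days this is 4.63 h/day, rounded up to 5.0. The article gives 389 h, 4.6 and 5.
- R = 0.2, A = 48: (18.150 + 3.224 − 6.480)² = 222 h.
- R = 1.0, A = 48: (18.150 + 16.122 − 6.480)² = 772 h.

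At fixed type and age, the dose still rises about 3.5-fold (772/222) across this severity range. Type and age therefore do not absorb severity. With severity uniform on 0.2 to 0.8 or 0.2 to 1.0 logMAR, ages 36 to 107 months and equal shares of the three types (all assumed), severity and prescribed dose correlate 0.82 to 0.89 in the standardized arm. In the personalized arm the correlation is 0.50 to 0.55 overall and 0.42 to 0.78 within type.

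**2. Size of the bias in large samples.** For a linear model the bias in the dose slope is b × δ. Here b is the gain per logMAR of starting deficit, and δ is the coefficient of dose when severity is regressed on dose, type and age. I used 200,000 simulated children, both dose rules, mean compliance about 45% (the Discussion says that less than half is received), and the initial prescription held for 84 days.

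| Severity range; spread of compliance | δ (logMAR per 100 h) | bias, b = 0.2 | bias, b = 0.4 | bias, b = 0.6 |
|---|---|---|---|---|
| 0.2–1.0; moderate | about 0.115 | 0.023 | 0.046 | 0.069 |
| 0.2–0.8; wide | about 0.045 | 0.009 | 0.018 | 0.027 |

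These rows are the extremes of the four combinations run. A true slope of 0 is estimated at 0.009 to 0.069, and a true slope of 0.05 at 0.059 to 0.119. With severity in the model both true values are recovered (about 0.00 and 0.05).

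**3. Size at the trial's sample size.** Assumptions: n = 120 split between the arms, no true dose effect, 12 weeks, wear uniform 0 to 90%, severity uniform from 0.2 to an upper limit of 0.6, 0.8 or 1.0 logMAR, gain 30 to 50% of the deficit, noise SD 0.1.

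- Dose, type and age only: false slope about 0.01 to 0.04 logMAR per 100 h, rejection about 14 to 83%.
- Severity added: slope about 0.000, rejection 5 to 6%.
- If treatment length varies independently of response: false slope 0.004 to 0.02, rejection 8 to 49%.

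The assumed severity range matters most. A separate run under the 12-week assumptions, with fortnightly updating of the personalized dose and a purely computational cap of 12 h/day, gave:

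| Upper limit of severity | false slope per 100 h | rejection |
|---|---|---|
| 1.0 | 0.024–0.038 | 59–84% |
| 0.8 | 0.013–0.024 | 17–42% |
| 0.6 | 0.010–0.017 | 11–21% |

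Its extremes (11 and 84%) agree with 14 to 83% to within simulation error and coding detail.

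**The case against.** The best defence is that the Analyses section gives no model equation. It names an objective and leaves the technique open, and covariates are commonly left to an analysis plan that is not shown. The authors plainly regard severity as relevant, since their own dose model contains it. This stands in part: a reader might infer that a fixed three-term model has been committed to, and the text does not go that far. What it does show is a stated factor list that omits severity and conflicts with the abstract. That is a fault in what the article states, and it would need correcting even if an unseen plan adds the term.

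Three stronger readings are tempting and are not supported.

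- **A false slope is almost certain.** If every child were dosed by the standardized rule, with severity uniform on 0.15 to 1.0 logMAR and wear 10 to 90%, the false slope would be 0.048 to 0.080 and significant in 94 to 100% of trials. But half the trial is personalized, where dose also follows age and type, which are in the list. The documents do not give the severity range either. This is near a worst case.
- **The slope will feed directly into later dosing models.** No section says so. The Discussion mentions future modifications only in connection with dose monitoring, and the existing formula already includes severity.
- **Stopping on response adds to the same bias.** Slow responders do accumulate more hours, but that may pull the slope down. It was not simulated, so the net effect of both mechanisms is not established.

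**Conclusion.** The concern holds for a secondary objective. The abstract and the body state different factor lists, and the body's list leaves out a variable that sets dose in both arms and limits gain. Fitted as listed, the regression biases the dose slope upward through severity whenever gain rises with starting deficit. Under the n = 120 assumptions above the bias is about 0.01 to 0.04 logMAR per 100 h over 12 weeks, with false-positive rates from roughly three times nominal (14% against 5%) up to 83%. It disappears once severity is included.

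The direction follows from the design. The size rests on the assumed severity distribution, wear, strength of the link between deficit and gain, and noise. The simulations also use one severity value for both dose rules, whereas the article bands the standardized arm by acuity and uses residual amblyopia in the personalized formula. The randomized comparison of time to best acuity does not use this regression and is unaffected.

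**What to change.** Make the Abstract, the Objectives of the study and the Analyses section list the same factors: monitored dose, severity at the start of occlusion, amblyopia type and age. Say which severity measure is meant (amblyopic-eye acuity or residual amblyopia) and enter it as a continuous covariate. Its interaction with type, as in the article's own dose formula, is optional.

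Since treatment ends on response or stabilization, state that total dose to exit will be interpreted with caution. An analysis of dose and acuity over a fixed window could be added as a sensitivity analysis. It answers a somewhat different question, so it should not replace the main regression.

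The cost is a change of wording. Acuity at the end of optical treatment is already needed to assign the dose, and monitored dose is read at the scheduled visits. The price is a somewhat wider interval for the dose slope, because dose and severity are correlated.

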To illustrate implementation, consider a hypothetical patient who enters occlusion aged 48 months with residual amblyopia of 0.5 logMAR and amblyopia associated with anisometropia. Using the formula derived from our model, the estimated total effective dose would be 389 hours. Over a 12-week follow-up period, this requires an average daily dose of 4.6 hours per day, and so we initially prescribe 5 hours of occlusion a day. At a follow-up appointment 2 weeks later, the patient has only undertaken 30 hours of occlusion (rather than the prescribed 70). The patient’s total effective dose reduces from 389 to 359 hours, but with only 10 weeks left of the initial follow-up period the patient must now average 5.1 hours of occlusion a day. Thus, our prescribed dose-rate increases to 5.5 hours a day.

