### Endpoint determination and sample size calculation

Participants complete the trial at that point in the occlusion phase at which equal visual acuity of each eye is achieved, or if vision has stabilized (defined as three inflexions in a plot of acuity against time or remaining unchanged over three consecutive visits). All children wear occlusion for a minimum of 6 weeks before discontinuing if no significant gains in visual acuity are observed. A sample size of 60 in each arm at 95% power and with a type I error rate of 0.05 corresponds to a Cohen’s *d* statistic of 0.605. The log-transformed time to best visual acuity across MOTAS [11] and ROTAS [12] was approximately normally distributed and had a mean (standard deviation) of 4.0133 (0.801). We could therefore expect to detect a difference of around 21 days in mean time to best visual acuity in our two groups.

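### The factors listed for the acuity-change regression omit severity, which the abstract names and which feeds the prescribed dose in both arms; a model built on that list is biased towards showing a dose effect.

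*Protocol article*

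**What the plan says.** Three places in the protocol article describe the same secondary objective.

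- Objectives of the study: change in logMAR acuity is to be related to "Objectively monitored occlusion dose,Type of amblyopia,Age of participant".
- Analyses: the "relationship between changes in visual acuity and dose, amblyopia type, and age, will be investigated using standard regression modelling approaches".
- Abstract, Methods/design: change in acuity is to be related "with age, amblyopia type, and severity of amblyopic visual acuity deficit".

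The first two name dose but not severity. The third names severity but not dose.

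The dosing sections tie dose to severity. In the standardized arm, "participants are prescribed one of three dosing regimens dependent on their visual acuity at the end of the optical treatment phase": 2, 3 or 5 hours a day for acuity below 0.4, from 0.4 to below 0.8, and 0.8 logMAR or worse. In the personalized arm, "participants are prescribed an initial occlusion dose determined by their age, type, and severity of amblyopia"; the formula contains residual amblyopia, and "dose-rates less than 2 hours per day are never prescribed". The endpoint section ends a child's participation at the point "at which equal visual acuity of each eye is achieved", or once vision has stabilized.

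**The concern.** A variable that influences both the exposure and the outcome, and is left out of the regression, biases the exposure coefficient. Severity fits that description on the article's own account. It is fixed before the first patch is prescribed, it enters the dosing rule in each arm, and it limits the outcome because a child with a small deficit has little to gain before the eyes are equal. It precedes dose, so it is not a step between dose and gain, and adjusting for it does not remove any of the dose effect.

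Randomization does not protect this analysis. The regressor is hours recorded by the monitor, which depend on the prescribed rate, compliance and duration. Only the dosing strategy is randomized.

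Monitored dose is the first factor listed under the first secondary objective. An inflated coefficient would overstate the acuity gained per hour of patching.

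**Working it through.** **1. Reproduce the article's dose figure.** The formula in Personalized dosing strategy, with the age coefficient read as 0.135, for an anisometropic child of 48 months and residual amblyopia 0.5:

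(18.150 + 16.122 × 0.5 − 0.135 × 48)² = 19.731² = 389.3 h.

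The article says "the estimated total effective dose would be 389 hours", so the reading is right. Over 84 days this is 389.3 / 84 = 4.6 h a day, also as stated.

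**2. How far severity moves the prescription.** Same formula at 48 months, residual amblyopia 0.2 against 0.8:

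| Type | At 0.2 | At 0.8 |
|---|---|---|
| Anisometropic | 14.894² = 222 h | 24.568² = 604 h |
| Mixed | 15.032² = 226 h | 17.400² = 303 h |
| Strabismic | 13.816² = 191 h | 16.688² = 279 h |

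Dose rises with severity for every type, steeply only for anisometropia. In the standardized arm the bands give 2 × 84 = 168 h, 3 × 84 = 252 h and 5 × 84 = 420 h over 12 weeks at full wear.

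**3. Direction of the bias.** In a linear model the dose coefficient without severity equals the coefficient with severity plus γδ. Here γ is the effect of severity on gain given dose, type and age, and δ is the slope of severity on dose given type and age. The dosing rules make δ positive. If worse eyes have more to gain, γ is positive too, and the bias is upward. If γ is zero, there is none.

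**4. Size, by simulation.** Taken from the article: 60 children per arm, both dosing rules, the 2-hour floor, and log time to best acuity with mean 4.0133 and SD 0.801 for variable duration. Assumed, because the article does not give them: severity uniform on 0.15 to 1.0 or gamma-distributed; ages 36 to 107 months; equal mix of types; mean wear 45% (the Discussion says less than half) or 70%; residual SD 0.10 logMAR, or measurement error as stated below. Each scenario had 1,000 to 2,000 trials. Gain was regressed on received dose, type and age, without and then with starting severity.

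Severity correlated 0.84 to 0.87 with the prescribed rate in the standardized arm, 0.57 to 0.59 in the personalized arm, and 0.24 to 0.59 with received dose.

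Share of trials with p < 0.05 for dose when hours do nothing:

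| How gain arises | Severity omitted | Severity added (linear) |
|---|---|---|
| Unrelated to measured severity | about 5% | not needed |
| Only capped at the deficit | 6–54% | about 4–10% |
| No true gain, baseline measurement error SD 0.05–0.10 | 6–41% | about 4–6% |
| 30% of the deficit | 30–99% | about 4–6% |
| 50% of the deficit | 50–100% | about 4–6% |

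The follow-up assumption matters. In one cap-only setting (gamma severity, 70% wear) the rate was 46% with a fixed 12 weeks, 37% when duration was linked to severity and 16% when duration was unrelated to it. It was about 9% in all three once severity was added.

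A separately coded simulation with no dose effect gave 64% (fixed 12 weeks) and 29% (variable duration) for gain at 30% of the deficit, 13% and 8% for gain only capped, and 5–6% for gain unrelated to severity. Adding baseline severity brought these to roughly 4–8%.

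**5. Size when dose does work.** True effect 0.05 logMAR per 100 h, 30% severity-related gain, measurement error SD 0.07, 45% wear:

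- Fixed 12 weeks: 0.113 without severity (0.113 / 0.05 = 2.3 times the truth), 0.048 with it.
- Variable duration: 0.070 without severity (0.070 / 0.05 = 1.4 times), 0.050 with it.

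**The case against.** The strongest reply is that the article names factors of interest and does not lay down a closed covariate list. It says only that standard regression will be used, and a condensed article may leave baseline adjustment to a fuller document. The authors plainly know that severity matters: the Background says dose-response varies with it, and their dosing formula includes it with type interactions. This reply stands in part. A reader might infer that severity has been ruled out of the analysis, and the text does not say so. What remains is that the factors are stated twice without severity and once with it. Anyone who follows the objectives and analysis sections as written would fit the biased model.

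The second reply concerns size, and it stands. A reader might infer that the regression will show a dose effect even if patching does nothing. The documents do not support that. The exit rule supports a cap on gain, where the excess ranges from slight to large. The highest rates come from assuming that gain is proportional to the deficit, and no section gives such a figure. Fixed-window results also overstate the problem for a trial in which duration varies.

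Third, the steep anisometropic example should not stand for all types, and severity should not be called the main determinant of received dose. Correlations of 0.24 to 0.59 mean that it explains about 6% to 35% of the variance (0.24² = 0.058; 0.59² = 0.348). Compliance and duration also contribute.

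Fourth, a reader might suppose that the age and type coefficients are confounded in the same way because both drive dose. Both are already in the model alongside dose, so that argument fails. Omitting severity could affect them by another route, but this was not calculated.

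**Conclusion.** The point holds as a bias towards a dose effect and as an inconsistency between the abstract and the objectives and analysis sections. The direction follows from the article's own dosing and exit rules, provided that gain is related to measured severity. The size does not follow from the article. With no true effect, the false-positive rate runs from the nominal 5% to well over 50%, depending on how gain relates to severity, the spread of severity, noise, compliance and follow-up. It is lower under variable than under fixed follow-up. None of the simulations modelled exit triggered by response.

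Only a secondary, observational analysis is affected. A reader might extend the point to the comparison of time to best acuity between arms. That comparison is randomized and does not use this regression.

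**What to change.** In Objectives of the study and in Analyses, add severity at the start of the occlusion phase as a covariate, and state which measure is meant (amblyopic-eye acuity or interocular deficit). A flexible form is preferable, since a linear term still left up to about 10% false positives in the cap-only case. Make the abstract list the same factors: dose, severity, type and age. Severity slopes that differ by type, as in the dosing formula, are an option and not a requirement. With baseline in a linear model, change and exit acuity give the same dose coefficient apart from sign, so the outcome can stay as it is.

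The cost is a wording change and one covariate, already measured because it sets the dose in both arms. The interval for the dose coefficient may be slightly wider in some cases. The adjustment does not remove confounding by compliance or by exit that depends on response, so the dose coefficient should still be reported as observational.
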